## Abstract

**Introduction:**

Even if indications for mastectomy have been progressively reduced in loco-regional breast cancer (BC) treatment, the harmful effects of surgery are still numerous and can impact physical and psychological wellbeing of women. The RIPOSTE (Reconstruction, self-Image, Posture, Oncology, “Santé”-Health, Therapy, “Escrime”-Fencing) program aimed to propose adapted fencing to patients with BC. This study aims to investigate the effect and conditions of effectiveness of the RIPOSTE program.

**Methods and analysis:**

This is a prospective randomized controlled trial including 24 patients with invasive BC who have just undergone surgery. The study will be proposed to the patient and if interested, the patient will be referred to a sports physician for a medico-sportive evaluation. At the end the evaluation, if the patient meets the inclusion criteria, she will be randomly assigned to one of the 2 groups based on a 1:1 principle: *Early RIPOSTE group* (receive one fencing session per week for 3 months immediately after their inclusion), *Delayed RIPOSTE group* (receive one fencing session per week for 3 months but within the 3 months following their inclusion). Patients will be included for 6 months with 3 follow-up times (0, 3, and 6 months) by a sport physician. The primary outcome is the evolution of quality of life score. Secondary outcomes are disability score, fatigue, anxiety-depression, cost-effectiveness and process evaluation.

**Ethics and dissemination:**

The study protocol has been approved by a French ethics committee (CPP Sud Méditerranée IV, N°ID-RCB: 2020-A01916-33). Results will be submitted for publication, at scientific conferences and through press releases.

**Trial Registration:**

NCT04627714.

## Introduction

Despite national cancer screening programme organized since 2004, breast cancer (BC) still affects many women in France (Jooste et al., 2011). Recent therapeutic improvements have significantly improved the survival rate of patients (89% of 5-year survival rate). Surgery is the essential treatment for BC at the loco-regional stage. Even though the indications for mastectomy have been gradually reduced and conservative surgery is more frequently possible, the harmful effects of surgery are still numerous (pain, mobility problems, oedema…). Surgical scars can hamper the mobility of the arm and posture is very often changed after mastectomy (for example, the shoulder may lower and become internally rotated and back pain is also frequently found) (Rostkowska et al., 2006). Lymph node expertise by sentinel procedure as well as lymph node axillary dissection are also frequently reported as possible causes of postoperative pain and joint amplitude reduction. In addition to surgery, adjuvant treatments are also involved in numerous adverse effects enhancing pain. For instance, radiotherapy may increase the risk of lymphoedema and the use of aromatase inhibitor hormone therapy has been associated with possible risk of arthralgia.

Many studies have shown that the side-effects of the various treatments (e.g., pain in the treated area, redness of the skin, oedema of the breast, nausea, fatigue…) lead to a deterioration in the Quality of Life (QoL) of patients (Browall et al., 2008; Montazeri, 2008). This mainly concerned the areas of physical functions, daily activities, and body image. An increase in symptoms (fatigue, dyspnoea, pain, nausea/vomiting and constipation) as well as high anxiety/depression were also observed (Reich et al., 2008).

Literature have shown benefits of regular physical activity (PA) during and after BC treatment, particularly in terms of improving the quality of life (QoL) (Manneville et al., 2018). Several randomized controlled trials have shown that appropriate physical activity (PA) during and after cancer treatment improved patients' QoL (Mishra et al., 2012a,b). However, further studies are needed to determine the optimal type and timing of exercise (Desnoyers et al., 2016).

With 119 Olympic medals since the modern Olympics began in 1896, fencing is France's number one Olympic sport. The relevance of fencing as PA in the context of BC has been suggested quite naturally (both by patients and the medical profession) during the various consultations in the management of this pathology. The aim of fencing is to hit the opponent and avoid being hit back. Its practice thus makes it possible to acquire (or to maintain) the desire to fight and to win. Created in 2014 by [name] (MD, Toulouse, France), the RIPOSTE (Reconstruction, self-Image, Posture, Oncology, “Santé”-Health, Therapy, “Escrime”-Fencing) program aimed to propose adapted fencing to patients with BC (Leroy, 2017; Meyer et al., 2017). The program is under the governance of a scientific committee responsible for the deliverance of the RIPOSTE Label. To obtain this RIPOSTE Label, professional fencing masters have to complete a specific course of 3 days, renewed every 2 years, and to adhere to a 10 points chart (dedicated fencing clothing and material, free of charge for patients, under medical supervision). Adapted fencing is performed using the saber, always held on the operated side (sometimes involving change in laterality). The choice of the saber is important because this weapon is light and allows a large range of motion of the injured side during attacks, parries and ripostes.

An evaluation of the effectiveness of this programme and the most opportune period for its implementation is necessary to justify its maintenance and extension on a national and international scale. Before setting up a large-scale study, a pilot study on the expected effect and conditions of effectiveness of the RIPOSTE program is necessary.

### Research Hypotheses and Objectives

#### Hypotheses

Adapted and secure fencing and its' early implementation in immediate poste-surgery may be an effective way of improving or reducing deterioration of physical and psychological health in patients operated for BC.

#### Main Objective

The main objective is to compare immediate post-surgical fencing (ERG: Early RIPOSTE group) vs. delayed fencing (DRG: Delayed RIPOSTE group) on 6-month evolution of global QoL score of patients operated for invasive BC.

#### Secondary Objectives

(SO1) Compare ERG vs. DRG on the 6-month evolution of several secondary criteria of patients operated for invasive BC: other dimensions of QoL, disability of the lateral arm, fatigue and anxiety-depression.(SO2) Compare early (3-months) effectiveness of fencing (fencing vs. no fencing) on physical and psychological health of patients operated for BC.(SO3) Identify 6-month trajectories of QoL, disability of lateral arm, fatigue and anxiety-depression and theirs associated factors.(OS4) Evaluate retrospectively the conditions of effectiveness of RIPOSTE (qualitative interview).

## Methods and Analysis

### Design of RIPOSTE Trial

A prospective randomized controlled trial including patients with invasive BC who have just undergone surgery from 3 centers in Northeastern France (CHRU Nancy, Institut Lorrain de Canérologie and HIA Legouest Metz). The study will be proposed to the patient by the oncologist or surgeon after surgery. If interested, the patient will be referred to a sports physician for a medico-sportive evaluation.

#### Inclusion Criteria

A woman aged at least 18 years;Undergone unilateral breast surgery for primary invasive breast cancer;2–4 weeks after surgery;Accept and be able to complete the self-administered questionnaires;Satisfy the prior medico-sportive evaluation;Informing and signing informed consent.

#### Exclusion Criteria

Presence of bone metastases, especially vertebral metastases;Presence of a contraindication to the practice of fencing at the time of the medico-sport evaluation;Refusal to participate in the study.

### Recruitment and Randomization

The study is to be initiated from September 2021 with an anticipated end for subject recruitment in November 2021. Study completion is scheduled for June 2022.

The study will be proposed to the patient by the oncologist or surgeon after surgery. If interested, the patient will be referred to a sports physician for a medico-sportive evaluation. At the end the evaluation, if the patient meets the inclusion criteria, she will be randomly assigned to one of the 2 groups based on a 1:1 principle using automatic software Ennov^®^ (Figure 1):

**Figure 1 F1:**
[figure not shown]
Design of the ≪Solution RIPOSTE≫ trial.

#### Early RIPOSTE Group

Patients in this group will receive one fencing session (1–1.5 h/session) per week for 3 months immediately (within 2 week) after their inclusion. A maximum of 12 sessions.

#### Delayed RIPOSTE Group

Patients in this group will receive one fencing session (1–1.5 h/session) per week for 3 months but within the 3 months following their inclusion. A maximum of 12 sessions.

### Interventions

Once a week, for a duration of 1–1.5 h/session, and during a complete sport season, a group of 10–12 patients practiced adapted fencing. Following a warm up time dedicated to muscle awakening and progressive cardio-respiratory solicitation, patients then started specific fencing exercises from fundamental footwork (advance, retreat, lunge) to actions involving the injured side that holds the saber. Fencing is adapted in so far as all offensive and defensive actions are performed with respect of the mobility of the shoulder. Primary (tierce = outside; quarte = inside; quinte = head) and secondary parries are therefore executed by patients with the highest mobility but without ever causing pain. Coordination, agility and strength are trained during exercises between patients and during lessons with the fencing master. The adapted fencing session finished with a cool down period and a final salute.

### Ethical Approval

Verbal informed consent will be obtained from each participant and they will be allowed to withdraw at any time without any consequences. Data will be made anonymous and only the first letter of the first name and surname and a number attributed to each patient will be recorded. This research complies with the Helsinki declaration and is registered and received ethical authorization by the French committee for individual protection (CPP Sud Méditerranée IV, N°ID-RCB: 2020-A01916-33). This research is registered on clinicaltrials.gov (NCT04627714).

### Follow-Up Visits

Patients will be included for 6 months with 3 follow-up times (0, 3, and 6 months) by a sport physician.

#### Inclusion

Prior to any examination or act specific to the research, the sports physician will inform the patient and obtain her free, informed and written consent. During this visit, after obtaining the patient's written consent, a medico-sportive evaluation will be carried out for each patient by a sports physician to assess her physical conditions for the practice of fencing (assessment of shoulder mobility using the Constant index and evaluation of surgical adhesions) and to detect any contraindications to the practice of fencing. If the medico-sportive evaluation is not satisfactory or if any other inclusion or non-inclusion criteria are not met, the patient will not be included in the study. If all inclusion and non-inclusion criteria are met, the sports physician will proceed with randomization. At the end of this visit, a CRF will be given to the patient to complete the various inclusion questionnaires. She will be offered an appointment for the visit at 3 months regardless of the group in which she is randomized.

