#### Month 3 Visit

For patients of the DRG, it will confirm the absence of contraindications to the practice of fencing before the beginning of the sessions within 8 days. At the end of this visit, medical data such as complementary treatments (pain treatment, anti-diarrhea, antiemetic's, psychotropic drugs, treatment not declared to the doctor), weight gain, presence of lymphedema, co-morbidities and patient-reported outcomes will be collected for all patients whatever the intervention group. An appointment for the visit at 6 months will be offered to each patient regardless of the group.

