#### Outcomes

The primary outcome is the evolution of QoL score. Secondary outcomes are disability score, fatigue, anxiety-depression, cost-effectiveness and process evaluation.

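### The baseline quality-of-life score of the primary change endpoint is collected after randomisation, from patients who cannot be masked to their arm

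*Protocol article*

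**What the plan says.** The protocol article gives the order of the inclusion visit in the Inclusion subsection of Follow-Up Visits. After written consent and the medico-sportive evaluation comes randomisation: "If all inclusion and non-inclusion criteria are met, the sports physician will proceed with randomization". The next step is the baseline forms: "At the end of this visit, a CRF will be given to the patient to complete the various inclusion questionnaires". The sentence after that takes the group as already assigned: "She will be offered an appointment for the visit at 3 months regardless of the group in which she is randomized".

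Recruitment and Randomization gives the same order, with no questionnaire step before allocation: "At the end the evaluation, if the patient meets the inclusion criteria, she will be randomly assigned to one of the 2 groups".

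The arms differ in when fencing begins. The early group starts "immediately (within 2 week) after their inclusion". For the delayed group, the Month 3 Visit subsection (counting in days) says: "For patients of the DRG, it will confirm the absence of contraindications to the practice of fencing before the beginning of the sessions within 8".

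Under Outcomes, "The primary outcome is the evolution of QoL score". Patient Reported Outcomes makes this a self-completed measure (EORTC QLQ-C30 with BR23). Statistical Analysis compares the average 6-month change between arms, by a univariate test and by a mixed model that uses M0, M3 and M6.

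**The concern.** A baseline should be measured before anything that differs between the arms can act on it. Here the differing event is the news of the allocation: fencing now, or fencing in about three months. The instruments scored after that news include emotional wellbeing, global health, fatigue, and anxiety and depression, all of which could respond to it.

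Randomisation balances what existed before allocation. It gives no protection against a distortion that arises afterwards. If M0 moves differently in the two arms, the change from M0 moves with it, even if fencing has no effect. The same applies to change in the DASH, MFI-20 and HADS scores and to the latent class trajectories, which also start at M0. With no score taken before allocation, no later analysis can recover the true baseline. The pilot's results are also meant to refine the size of the main trial, so a distorted change estimate, and the visit order itself, could be carried forward.

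**Working it through.** **1. Order of events.** The two sections that describe the visit agree:

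| Step | Inclusion (Follow-Up Visits) | Recruitment and Randomization |
|---|---|---|
| Medico-sportive evaluation | yes | yes |
| Eligibility confirmed | yes | yes |
| Randomisation | next step | next step |
| M0 questionnaires | end of visit, after randomisation | not mentioned |

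No section puts the questionnaires before randomisation, delays disclosure, or describes masking.

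**2. How an M0 shift enters the contrast.** Let d be the between-arm difference in M0 caused by knowing the allocation, and p the part of it still present at M6.

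- Contrast in change = (M6 − M0) in the early arm minus (M6 − M0) in the delayed arm.
- Bias = p − d. A shift that has gone by M6 (p = 0) gives a bias of −d. A shift that persists in full (p = d) cancels.
- With baseline adjustment and p = 0, the bias is about −rho × d, where rho is the M0–M6 correlation (equal SDs).

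**3. The plan's yardstick.** Inputs from Sample Size: alpha 5% (taken as two-sided), power 80%, SD 10, stated detectable difference 8.26. With 24 patients at 1:1 there are 12 per arm.

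- Normal approximation, 12 per arm: (1.960 + 0.842) × 10 × √(2/12) = 11.44. Exact t: 11.97.
- Exact t, 24 per arm: 8.26.

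So 8.26 is reproduced only with 24 patients in each arm. That is a separate matter and this point does not depend on it; 8.26 is used below because it is the protocol's own figure.

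**4. Illustration.** The documents give no value for d. The values below are assumed, with p = 0. The last two columns use a two-sided t-test with 12 per arm and SD 10 for the change.

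| Assumed transient d (points) | d / 8.26 | Rejection rate with no true effect | Power at a true 8.26 if the shift opposes it |
|---|---|---|---|
| 0 | 0% | 5.0% | 49% |
| 2 | 24% | 7.6% | 31% |
| 3 | 36% | 10.8% | 23% |
| 4 | 48% | 15.5% | 17% |
| 5 | 61% | 21.6% | 12% |

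Against 11.97 instead of 8.26, d of 2 to 5 points is 17% to 42%.

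**5. With baseline adjustment.** For assumed rho of 0.3 to 0.7, the remaining bias runs from 0.3 × 2 = 0.6 points to 0.7 × 5 = 3.5 points: smaller, but not zero.

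**6. Length of the battery.** QLQ-C30 (30) + BR23 (23) + DASH (30) + MFI-20 (20) + HADS (14) = 117 items, before the short IPAQ and the socio-demographic questions.

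**The case against.** The best defence is that the harm is inferred. The article does not say when the patient learns her group, and it does not use the term open-label. A condensed account of a visit may not reflect the exact order in practice. Both arms are promised the same programme of up to 12 sessions, which may soften any reaction. This is a pilot of 24 patients limited by hall capacity, and the article already names its small size as a limitation.

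These arguments limit how much can be claimed, but they do not remove the point. The order is stated, two sections agree on it, and the wording leaves the route open. A reader might nevertheless infer more than the document supports:

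- **Some M0 forms are completed after a first fencing session.** This rests only on the absence of a return date, which an article may leave to the full protocol. The text leans the other way: month 0 is listed as a follow-up time, Data Collection places patient-reported outcomes at each follow-up, and posting forms home is mentioned only for patients who miss month 6.
- **Every outcome is affected.** Cost-effectiveness and process evaluation are also outcomes. The point concerns the questionnaire scores.
- **The bias runs against early fencing.** Disappointment in the delayed arm or optimism in the early arm would have that effect, but apprehension about starting soon after surgery would act in the opposite direction. The direction is unknown.
- **The whole shift always passes into the result.** Only the part that has faded by follow-up does.
- **Two to five points is an estimate.** It is an assumed range to show scale.

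**Conclusion.** The point holds as a weakness in the stated visit order. M0 quality of life, and the M0 disability, fatigue and anxiety-depression scores, are collected after randomisation from patients who cannot be masked, with nothing to keep the allocation from them until the forms are done. Disclosure before completion is an inference from that order, not a stated fact. The resulting bias in the change contrast equals the transient part of any arm-related shift; its size and sign cannot be determined from the document. If a transient shift of 2 to 5 points is assumed, it is large relative to the 8.26 points the trial says it can detect. The document does not show that such a shift will occur. The case for acting is that the route cannot be closed by analysis afterwards and is cheap to close beforehand.

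**What to change.** Reorder the Inclusion subsection of Follow-Up Visits, and align Recruitment and Randomization with it: consent; medico-sportive evaluation and confirmation of eligibility; completion and return of all M0 questionnaires at the visit; then randomisation by the sports physician. If the forms cannot all precede randomisation, the minimum is that they are returned before the patient is told her group. If the full protocol already works this way, the article's text should be corrected to say so.

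The cost is waiting time at the inclusion visit for at least 117 items plus the IPAQ and socio-demographic questions, which is more than a few minutes. No extra visit or staff is needed. A check in Ennov that the M0 forms have been received before allocation is released would be useful but is optional.

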#### Month 3 Visit

For patients of the DRG, it will confirm the absence of contraindications to the practice of fencing before the beginning of the sessions within 8 days. At the end of this visit, medical data such as complementary treatments (pain treatment, anti-diarrhea, antiemetic's, psychotropic drugs, treatment not declared to the doctor), weight gain, presence of lymphedema, co-morbidities and patient-reported outcomes will be collected for all patients whatever the intervention group. An appointment for the visit at 6 months will be offered to each patient regardless of the group.

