##### Disability

Disability the DASH (Disabilities of the Arm, Shoulder and Hand measurement tool) (Dubert et al., 2001), is a subjective self-assessment questionnaire for the overall functional capacity of the upper limbs. It evaluates from 30 items the ability to perform 23 activities, the severity of the symptoms and optional sporting or instrumental and professional activity. The entire questionnaire will be administered to the patient. The overall score is in the form of a score on 100 by the following calculation method: [(sum of n responses)−1] / n × 25. A high score indicates a high overall functional disability. The score is valid only if 90% of the questions were filled by the patient (i.e., 3 missing values at most).

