### Statistical Analysis

#### Quantitative Analysis

The primary analysis will be performed according to the intention-to-trait principle by comparing the 6-month average evolution of quality of life score between the two groups using mixed model for repeated data. The main criterion of the programme's effectiveness will be assessed by comparing average changes in the 6-month quality of life score between the two groups. An analysis of the missing data will be carried out and the randomness or otherwise of the missing data will be investigated (Diggle and Rubins classification). For the main analysis, a distinction will be made between two types of analysis:

Univariate analysis allowing the comparison of differences in quality of life scores between the two arms: non-parametric (Mann Whitney-Wilcoxon) and/or parametric (Student Test) methods.Multivariate analysis of the repeated customized analysis of variance type taking into account the adjustment and stratification variables (mixed models with consideration of repeated measurements and random center effects). These models make it possible to use not only the measurements at the two extreme times (M0 and M6) but also to take into account the measurement at the intermediate time (M3). They also make it possible to take into account the random center effect (the same intervention will not always have the same effect from one center to another). The SAS MIXED or GLIMMIX procedures will allow this analysis.

Other comparisons will use the same statistical methods for secondary judging criteria.

An analysis of the 6-month change profiles of the different dimensions of quality of life taking into account all monitoring times (0, 3, and 6 months) will be carried out using the Latent Class Growth Analysis (LCGA) methods (Jones et al., 2001; Jung and Wickrama Ka, 2008). This method makes possible to identify sub-groups of patients with distinct trajectories of progression within the entire sample. A comparison of the distribution of these trajectories will be made according to the intervention group.

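### Month 3 questionnaires are collected at the end of a visit that includes a fencing clearance check for the delayed arm only, exposing the secondary fencing versus no-fencing comparison (minor)

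*Protocol article*

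**What the plan says.** In the protocol article, the Month 3 Visit section opens with a step for one arm. For the delayed group, "it will confirm the absence of contraindications to the practice of fencing before the beginning of the sessions within 8 days". The next sentence gives the time of data collection: "At the end of this visit, medical data such as complementary treatments", and it ends by including the questionnaires for both arms: "co-morbidities and patient-reported outcomes will be collected for all patients whatever the intervention group". The section describes no check or clearance for the early arm, and does not place the questionnaires before the check.

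The Secondary Objectives section makes month 3 the time point for SO2: "Compare early (3-months) effectiveness of fencing (fencing vs. no fencing) on physical and psychological health of patients operated for BC". The Quantitative Analysis section defines the main criterion as the change in quality of life over 6 months. It adds that the mixed models also use the month 3 measurement, and that the trajectory analysis uses all three times.

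The outcomes are answered by the patient. The Disability section says that the DASH "is a subjective self-assessment questionnaire for the overall functional capacity of the upper limbs". The Quality of Life section describes QLQ-C30 answers as reflecting the patient's situation when the questionnaire is given.

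**The concern.** Patients know which arm they are in, and the outcomes are self-reported. Taken as written, a delayed-arm woman gives her month 3 answers after a physician has confirmed, or declined to confirm, that she can start fencing. An early-arm woman has no such step described at that visit. Reassurance about the shoulder, or disappointment at a refusal, could colour answers on quality of life, anxiety, fatigue or arm function.

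Month 3 is the only time at which a group that has not fenced is measured, because the delayed arm starts its sessions directly afterwards. A distorted comparator at that point cannot be recovered later. Randomisation does not remove an influence that the visit procedure itself attaches to one arm.

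**Working it through.** The plan gives no figure for the order of steps at this visit, so there is none to reproduce, and reordering changes neither sample size nor power. The check is a reading of the sections followed by short algebra.

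**1. The two arms at month 3, as described**

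| | Early arm | Delayed arm |
|---|---|---|
| Contraindication check described | no | yes |
| Questionnaires collected | end of visit | end of visit |
| Role in SO2 | fencing | no fencing |

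The only stated difference before collection is the check.

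**2. Effect on SO2**

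Let E0, E3 and D0, D3 be the mean scores at inclusion and month 3 in the early and delayed arms. Let b be the mean shift in the delayed arm's month 3 answers caused by the check.

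Observed contrast = (E3 − E0) − (D3 + b − D0) = true contrast − b.

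The shift passes through in full. If a fraction p of the arm is cleared, with mean shift c, and the rest are refused, with mean shift r, then b = p·c + (1 − p)·r. The documents give none of p, c or r. If c and r have opposite signs, the sign of b is undetermined.

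**3. Scale only**

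The values of b below are assumptions without support in the documents. Inputs: SD 10 points (Sample Size section) and 12 per arm (24 patients, 1:1). The standard error of the difference is 10 × √(2/12) = 4.08. The last column is the rejection rate of a two-sided 5% t test with no true effect.

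| Assumed b (points) | b / SD | Rejection rate |
|---|---|---|
| 0 | 0 | 5.0% |
| 1 | 0.1 | 5.6% |
| 2 | 0.2 | 7.6% |
| 3 | 0.3 | 10.8% |
| 5 | 0.5 | 21.6% |

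The table shows what a given b would do. It does not show that b differs from zero.

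**4. Effect on the primary contrast**

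- Simple change, M6 − M0: the weights on M0, M3, M6 are (−1, 0, 1), so b contributes 0 × b = 0.
- Mixed model with time as a category and complete data: the same contrast of means, so 0.
- Linear slope over 0, 3 and 6 months: deviations from the mean time are −3, 0, 3, with sum of squares 18. The weights are −3/18, 0, 3/18, so b again contributes 0. This also holds under the usual symmetric covariance structures.
- Routes by which b could enter: month 6 values are missing and month 3 informs them, or the group effect is averaged over visits (an equal average of months 3 and 6 would carry b/2).

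**The case against.** The article is a condensed account. Collected need not mean completed: the forms might be filled in at home or on arrival and only handed over at the end. The article does not say when the result of the check is told to the patient. Nor does it rule out an examination of the early arm, since a sports physician follows all patients at every visit. These are real limits and they lower confidence. Even so, the end of the visit is the only timing given, and the only check described is for one arm.

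The check is also not wholly new information. Every included patient has already passed the medico-sportive evaluation, and delayed-arm patients know from inclusion that they will fence. Most of the anticipation is built into an open delayed-start design and would survive any reordering. Only the increment from the examination and its verdict is avoidable. Sensitivity will also vary by instrument: the MFI-20, for example, asks about the preceding days.

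A reader might infer three stronger things, and the documents support none of them.

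- **That SO2 is biased by a definite amount, say 2 to 5 points.** No such figure can be derived, and the sign is open: clearance could hide a benefit of fencing, refusal could exaggerate one.
- **That the primary result is biased because month 3 enters the mixed model.** With complete data the contrast from inclusion to month 6 gives that measurement no weight.
- **That month 6 has the same fault.** The Month 6 Visit section describes evaluation and questionnaires for everyone, with no step for one arm.

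**Conclusion.** The point holds as a minor, avoidable weakness in the month 3 procedure. The text places patient-reported outcomes at the end of a visit whose only described check applies to the delayed arm, and those scores are the sole no-fencing comparator for SO2. That comparison is exposed to an influence of unknown size and direction.

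The conclusion assumes that the questionnaires are answered when the article says they are collected, and that the early arm has no equivalent check at that visit. If the full protocol says otherwise on either, the concern shrinks or disappears. The primary contrast is essentially unaffected when data are complete. The consequence is confined mainly to one secondary objective in a 24-patient pilot.

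**What to change.** Amend the Month 3 Visit section so that all patients in both arms complete the questionnaires on arrival, before any examination, contraindication check or feedback from the sports physician, with the medical data collected afterwards. The check itself, and who may start fencing and when, stay as they are. Month 6 needs no change on this ground.

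The cost is one sentence in the visit procedure, with no extra visit, staff or data. The change removes the influence of the check and its result on the month 3 answers, but not the anticipation that comes from knowing the allocation. That should be acknowledged when SO2 is interpreted.
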